#### 3. Dependent variable

*Neuropsychiatric symptoms*. Assessment of neuropsychiatric outcomes will comprise three different measures including: objective cognitive task, parental proxy report and participant’s self-report.

1. A cognitive task (Go/No-Go) will examine response inhibition (RI), a central component of executive control [62], which is considered a sensitive measure for underlying risk for neuropsychiatric symptoms [63].

2. Proxy report—parents will complete the Child Behavior Checklist (CBCL) from the Achenbach System of Empirically Based Assessment (ASEBA) [64], which is considered a “gold standard” tool for assessing psychopathology among children and adults and has been used among pTBI patients [20, 23, 65].

3. Self-report–Emotion regulation questionnaire for children/adolescents (ERQ-CA) [66] and the response to positive affect scale for children (RPA-C) [67] will be used to examine participants’ perception of their own emotional regulation skills. These two forms of emotion regulation depend upon interactions between prefrontal and cingulate control systems, cortical and subcortical emotion generative systems [68], and are associated with neuropsychiatric symptoms [69].

#### 4. Covariates

*Pre-injury factors*. Demographic information regarding family’s socioeconomic status (SES), maternal educational level, ethnicity and religiosity will be collected at T0. Since Parents’ mental health pre and/or post injury may also affect a child’s neuropsychiatric status [70, 71], the General Health Questionnaire (GHQ-12) [72] will be used as a proxy of parents’ mental health. Parent’s will complete the CBCL at admission to reflect pre-injury functioning.

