### Research design

The proposed study will use a longitudinal prospective design and follow females after pTBI and age matched healthy female controls, aged 9 to 16 years [47]. Participants will be followed from admission to 18 months post injury. Participants will undergo an MRI protocol, a short neuropsychiatric assessment and a clinical assessment of puberty stage and hormonal level, across two time points: **Acute (T0)**: within one month post injury; **Chronic (T1)**: 18 months from T0 (sufficient time for neuropsychiatric changes post pTBI [48]). For a description of the schedule of study’s enrolment and assessment periods see S1 Table.

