### Measures of study variables

#### 1. Independent variable

*Clinical TBI group*. Participants will include females following mild to moderate-severe injuries. Patients will be recruited from the Pediatric Emergency Department, which treats ~200 children diagnosed with mild- TBI annually with ~30% females, and from Pediatric Rehabilitation Departments (PRD) of both Edmond and Lily Safra Children’s Hospital, Sheba Medical Center and Loewenstein Hospital, Israel. Each department treats ~35 pTBI patients annually with ~30% females.

Injury severity will be defined based on a composite index according to child’s Glasgow Coma Scale (GCS), Duration of Post Traumatic Amnesia (PTA) and duration of Loss of Consciousness. As no single measure of injury severity has been found to be reliable among children, using an index score will allow us to define injury severity as a continuous variable ranging from complicated-mild to severe with greater accuracy.

*Healthy control group*. Healthy age matched female participants will be recruited from the general population or from siblings of pTBI females.

Inclusion criteria: 1. for pTBI: All injury severities; 2. For both pTBI and healthy controls: Females aged 9–16 years (based on the 95%CI of age range sensitive for attaining pubertal milestones) [47]. Exclusion criteria for both groups: 1. History of neurological disorders, intellectual disorders, developmental disorders or previous head injury; 2. Cardiovascular instability; 3. Fever or evidence of microbiological contamination; 4. Uncontrolled seizures; 5. MRI exclusion criteria, such as metal implants. 6. Endocrinology exclusion parameters: known abnormality of gonadotrophin secretion or of ovarian function. In addition, all MRI scans will undergo a neuroradiological examination, and abnormal findings (aside from their brain injury for the pTBI group), will be reported to the Institutional Ethics Committee as well as to the participant. Following this, participant’s participation in the study will be stopped.

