#### Descriptive statistics

Descriptive statistics of variables will be obtained to understand the characteristics of the study population, to evaluate the distribution of participants across subgroups (e.g., puberty stage), and to identify potential confounders to inform subsequent analyses.

**Aim 1**- **moderated-mediation model:** To test our main study’s hypothesis we will apply a moderated- mediation model. Briefly, we will examine whether the magnitude of a mediation effect impact of mediator (*changes in brain network connectivity*) on the association between predictor (*pTBI*) and outcome (*neuropsychiatric outcomes*) is conditional on the value of a moderator (*puberty stage at T0*). The analysis of the moderated-mediation model will use Hayes’s (2013) PROCESS macro (Model 59) [73]. Bootstrapping method will test significance of the effects to obtain robust standard errors for parameter estimation [73]. This will produce 95% bias-corrected confidence intervals of these effects from 1000 resamples of the data. Confidence intervals that do not contain zero indicate significant effects at *p* < .05.

**Aim 2- effect of changes in puberty stage and hormonal levels on mediator and outcome:** Two step-wise linear regression models controlling for age and pre/post-injury factors in the 1st step; for the injury severity in the 2nd step; and for puberty stage and hormonal levels at T0 and T1, as well as the difference between both measures (i.e., *Δpuberty stages and Δhormonal levels*) in the 3^rd^ step, to predict (1) brain network connectivity and (2) neuropsychiatric outcomes, at T1 will be conducted.

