#### Secondary analyses

For all analyses, an equal distribution assumption of potential confounders (participants’ age, injury severity, time since injury, and pre/post-injury factors) will be tested and models augmented with terms for these confounders will be considered.

Puberty stage: in our primary analyses, we will use a binary puberty score (pre/post pubescence). Secondary analyses will consider each of the puberty measures (PDS, hormonal levels, Tanner stage) separately.

Neuropsychiatric outcomes: our primary analyses will use a composite global neuropsychiatric risk score based on the ASEBA Summary scales as our main outcome. In secondary analyses, we will consider each of the neuropsychiatric measures (IR, ASEBA, Emotional Regulation) separately.

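### The primary Aim 1 model does not commit to adjusting for the pre-injury CBCL, and leaves that choice to a weak balance test

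*Protocol article*

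**What the plan says.** The section 4. Covariates has parents "complete the CBCL at admission to reflect pre-injury functioning". The section 3. Dependent variable identifies the CBCL as the parent form of the ASEBA system. Under Secondary analyses the article states that "our primary analyses will use a composite global neuropsychiatric risk score based on the ASEBA Summary scales as our main outcome".

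For Aim 1, "The analysis of the moderated-mediation model will use Hayes’s (2013) PROCESS macro (Model 59"; the predictor is pTBI, the mediator is change in connectivity, the moderator is puberty stage at T0, and no covariate is named. The Aim 2 regressions in the same section do adjust, "controlling for age and pre/post-injury factors in the 1st step".

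The only adjustment rule that reaches Aim 1 stands under Secondary analyses and is worded to cover every analysis. Equal distribution of participants' age, "injury severity, time since injury, and pre/post-injury factors) will be tested", and "models augmented with terms for these confounders will be considered".

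Controls are age matched and "will be recruited from the general population or from siblings of pTBI females".

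**The concern.** Group membership is observed, not assigned. If girls with and without pTBI already differ in behaviour before the injury, and pre-injury behaviour predicts behaviour at T1, an unadjusted model counts part of that difference as an effect of pTBI. The article collects the variable needed to deal with this, but does not commit its main hypothesis test to using it.

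The rule it does state is weak in two ways. A significance test of balance has little power at this sample size, so a non-significant result gives little reassurance. Augmented models are then only to be considered, which leaves the choice open until the data have been seen. A strongly prognostic baseline score also improves precision when the groups happen to be balanced, and a balance test takes no account of that.

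The treatment of mediator and outcome is also uneven. The mediator is a T1 minus T0 difference and so refers to its own baseline. The outcome is not tied to its baseline in the Aim 1 model.

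**Working it through.** **Evaluable sample.** Sample size and power asks for at least 100 evaluable participants and expects about 20% attrition. The stated total is reproduced by 100 × 1.20 = 120. A 20% loss from 120 leaves 120 × 0.80 = 96, or 48 per group. I therefore use 48 to 50 per group.

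**Assumed inputs.** The article gives neither the correlation r between pre-injury and T1 scores nor the size of any pre-injury group difference d. I take r = 0.3, 0.5 and 0.7, with d = 0.3 SD as the worked case. Alpha is two-sided 0.05.

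**1. Power of the balance test.** In SD units the standard error of a group difference is √(2/n), and power ≈ Φ(d/√(2/n) − 1.96).
- n = 50, d = 0.3: 0.3/0.200 = 1.50, power 0.32.
- n = 48, d = 0.3: 0.3/0.204 = 1.47, power 0.31.
- n = 60 (all recruited girls, tested at T0), d = 0.3: 0.3/0.183 = 1.64, power 0.38.
- n = 50, d = 0.2: power 0.17. With d = 0.5: power 0.71.

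**2. Bias if the difference is left unadjusted.** Bias in the direct effect = r × d in SD units of the outcome. The type I error is for a simple two-group contrast with 50 per group (standard error 0.20) and no true effect.

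| r | bias at d = 0.3 | type I error |
|---|---|---|
| 0.3 | 0.09 SD | 0.073 |
| 0.5 | 0.15 SD | 0.117 |
| 0.7 | 0.21 SD | 0.183 |

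A simulation of the Model 59 outcome equation (N = 100, d = 0.3) gave unadjusted biases of 0.092, 0.152 and 0.208 SD. After the baseline score was added the bias was zero to within 0.001. The simulated baseline score was measured without recall error.

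**3. Precision in the outcome equation.** Residual variance is multiplied by 1 − r², and standard errors by √(1 − r²).

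| r | residual variance | fall in variance | fall in standard error |
|---|---|---|---|
| 0.3 | 0.91 | 9% | 5% |
| 0.5 | 0.75 | 25% | 13% |
| 0.7 | 0.51 | 51% | 29% |

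In the same simulation, with an assumed mediator-by-puberty interaction of 0.5, power for that term rose from about 0.65 to 0.68, 0.78 and 0.90.

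**The case against.** The article condenses a fuller protocol and introduces the Aim 1 model as a brief account. It lists the admission CBCL under covariates, and its confounder clause covers all analyses. A reader might infer that the primary model excludes the pre-injury CBCL, or that pre-injury factors appear only in secondary work. The text supports neither. The clause permits adjustment in Aim 1, and Aim 2, one of the two stated aims, enters these factors in its first step. What stands is that the article states a rule for Aim 1 and the rule is poor. That is more than a detail left to another document.

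A reader might also infer that injury severity and time since injury make the balance test impossible, since controls have neither. The clause does not say which groups are compared. Both could be compared between pre- and post-pubescent girls within the pTBI group, so I do not press this.

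A third tempting reading is that adjustment amounts to a larger sample for the whole mediation test. The gain shown applies to the outcome equation only. The indirect effect also depends on the path from pTBI to connectivity change, for which no gain has been shown. At r = 0.3 the gain is small, and a low correlation is plausible for a recalled rating and an interval of at least 18 months.

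Finally, no document figure shows that the groups will differ before injury. Excluding neurological, intellectual and developmental disorders, and allowing sibling controls, should narrow any difference without removing it. The pTBI rating is made after the injury, and the article does not say when control parents complete theirs. Recall that differs between groups could leave or add some bias.

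**Conclusion.** The point holds in this form: the primary model does not commit to the pre-injury CBCL, and the stated trigger for adjustment would miss a 0.3 SD difference about two times in three. If such a difference existed and went unadjusted, the direct effect would be off by about 0.09 to 0.21 SD. The power figure rests on 48 to 50 girls per group. The bias and precision figures rest on an assumed r of 0.3 to 0.7, and the bias also on an assumed d of 0.3 SD. The review shows exposure to bias, not that bias is present. Fixing the covariate in advance is worth doing at the low end of the range as well, since it removes a choice made after seeing the data and costs almost nothing.

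**What to change.** State in the Aim 1 analysis that the T0 CBCL composite, scored on the same scale as the T1 outcome, is a fixed covariate in both the outcome and the mediator equation of Model 59. Use the pre-injury rating for pTBI and the first-visit rating for controls, and say when control parents complete it. Drop the equal-distribution test as the trigger for adjustment; baseline distributions can still be described.

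The cost is one or two degrees of freedom on data already planned, with no extra visit. The report should note that the pTBI rating is parental recall, so adjustment may not remove all confounding.

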### Analytical approach

The following analyses will be conducted on both pTBI patients and healthy controls:

#### Descriptive statistics

Descriptive statistics of variables will be obtained to understand the characteristics of the study population, to evaluate the distribution of participants across subgroups (e.g., puberty stage), and to identify potential confounders to inform subsequent analyses.

**Aim 1**- **moderated-mediation model:** To test our main study’s hypothesis we will apply a moderated- mediation model. Briefly, we will examine whether the magnitude of a mediation effect impact of mediator (*changes in brain network connectivity*) on the association between predictor (*pTBI*) and outcome (*neuropsychiatric outcomes*) is conditional on the value of a moderator (*puberty stage at T0*). The analysis of the moderated-mediation model will use Hayes’s (2013) PROCESS macro (Model 59) [73]. Bootstrapping method will test significance of the effects to obtain robust standard errors for parameter estimation [73]. This will produce 95% bias-corrected confidence intervals of these effects from 1000 resamples of the data. Confidence intervals that do not contain zero indicate significant effects at *p* < .05.

**Aim 2- effect of changes in puberty stage and hormonal levels on mediator and outcome:** Two step-wise linear regression models controlling for age and pre/post-injury factors in the 1st step; for the injury severity in the 2nd step; and for puberty stage and hormonal levels at T0 and T1, as well as the difference between both measures (i.e., *Δpuberty stages and Δhormonal levels*) in the 3^rd^ step, to predict (1) brain network connectivity and (2) neuropsychiatric outcomes, at T1 will be conducted.

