**Methods:**

A case-control longitudinal prospective design will be used. 120 female participants aged 9 to 16 years (N = 60 per group) will be recruited. In the acute phase (T0-1 month), participants will undergo an MRI protocol for brain connectivity, as well as a clinical evaluation for puberty stage and hormonal levels. In the chronic phase (T1-18-24 months), participants will complete a neuropsychiatric assessment in addition to the MRI and puberty evaluations. Hormonal levels will be monitored at T0 and T1. A moderation-mediation model will be used to examine the moderating effects of puberty on the association between pTBI and neuropsychiatric symptoms in female girls and adolescents, through the mediating effect of brain network connectivity.

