Studies of pTBI survivors have reported high prevalence of pituitary dysfunction related to hormonal deficiency (hypopituitarism) at 1–5 years post injury [38]. Interestingly, injury severity did not predict endocrine outcomes. In a recent study, p-TBI patients had about 3-times the risk of a central endocrine diagnosis compared to the general population. Moreover, females had a shorter time gap between the injury and the endocrine disorder compared to males [25]. Probable pubertal adolescent females (13–18 years) had a reduced mortality rate compared to males. These findings suggest that post-injury elevation in hormonal levels among young females may propose an opposite profile to the withdrawal hypothesis reported in adult TBI females.

The relationship between puberty and brain development is likely to be complex and nonlinear, and interacting with the distinct but synchronous effects of age [33]. There is evidence for brain structural development associated with pubertal maturation [39, 40] with different trajectories seen in males and in females [39, 41]. Evidence of a strong relationship between white-matter fiber density and age, sex, and puberty during development has been reported [42, 43]. Physical pubertal changes predicted patterns of changes in structural connectivity, and pubertal processes contributed to distinct changes in males and females across brain development [44]. Studies using structural brain network graph theory revealed an early separation between developmental trajectories of males and females, with male adolescents displaying higher structural intra-hemispheric connectivity and females displaying higher inter-hemispheric connectivity [45]. Although studies on brain connectivity and pubertal hormones are limited, there is evolving evidence for the hypothesis that sex-hormones are related to the microstructure of white-matter and that pubertal development may be associated with maturation of structural connectivity above and beyond chronological age [46].

Taken together, the current research question forms a moderated-mediation model using a longitudinal case-control design. The main aim of the proposed study is to examine the moderating effect of puberty (pre-and post-pubescence) in females, on the association between brain network connectivity and neuropsychiatric outcomes in girls with/without pTBI. Fig 1 illustrates the study’s conceptual model.

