### Aims and hypotheses

Based on the literature review, the present study proposes the following aims and hypotheses (as depicted in Fig 1):

**Aim 1**: Examine the moderating effect of puberty (pre- and post-pubescence) on the association between pTBI, brain network connectivity measures and neuropsychiatric outcome among females:

1.1. Examine the direct association between pTBI and neuropsychiatric outcome (Fig 1: direct effect c’ pathway). We hypothesize that females following pTBI will present poorer neuropsychiatric outcome as compared to healthy female controls.

1.2. Examine the relationship between pTBI and brain network connectivity measures (Fig 1: slope a pathway). We hypothesize that females with pTBI will present higher network connectivity measures and lower network efficiency compared to healthy female controls.

1.3. Examine the relationship between brain network connectivity measures and neuropsychiatric outcome (Fig 1: slope b pathway). We hypothesize that higher network connectivity measures and lower network efficiency will be associated with poorer neuropsychiatric outcome.

1.4. Examine the moderating effect of puberty on the mediated association between pTBI, brain network connectivity and neuropsychiatric outcome (Fig 1: mediation a*b pathway through moderator). We hypothesize that puberty will moderate the associations between brain network connectivity measures and network efficiency, and neuropsychiatric outcome in females post pTBI. That is, post-pubescence females compared to pre-pubescence females will show higher network connectivity measures, lower network efficiency and poorer neuropsychiatric outcome.

**Aim 2:** Examine the effect of changes in puberty stage and hormonal levels on brain network connectivity measures and neuropsychiatric outcome in pTBI females. We hypothesize that among females following pTBI, earlier changes in puberty stages (i.e. changes from one Tanner stage to another) and a significant increase in hormonal levels across recovery, will be related to higher network connectivity measures and lower network efficiency as well as to poorer neuropsychiatric outcome.

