### Sample size and power

Sample size was calculated on the basis of our primary hypothesis that puberty will moderate the associations between brain network connectivity measures, and neuropsychiatric outcome in females post pTBI. The bootstrap method for moderated-mediation models was used [49]. The bootstrap method, based on resampling, is useful for finding the standard errors and forming percentile-based confidence intervals (CIs) for estimates when their sampling distributions are unknown. According to Preacher, Rucker & Hayes (2007), a minimum of 100 participants are required in order to achieve power of at least .80, at a significance level of α = .05, with a Cohen’s d medium effect size (corresponding to a value of 13% of the variance in predicted variable [50]; and in accordance with previous studies on neural correlates of neuropsychiatric outcomes in children with TBI [51]). Based on the literature on longitudinal studies with pTBI patients, and due to technical issues such as unusable scans due to excessive movement anticipated in a pediatric study, we anticipate an attrition rate of ≈20% [52]. Thus, 120 female participants will be recruited: 60 with pTBI and 60 healthy controls.

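### The primary moderation hypothesis is stated as two different contrasts, and no single Model 59 effect is named as the one that decides it

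*Protocol article*

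**What the plan says.** The protocol article places the deciding moderation effect as follows.

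**On the connectivity-to-outcome path (path b)**
- Introduction, main aim: puberty acts "on the association between brain network connectivity and neuropsychiatric outcomes in girls with/without pTBI", so patients and controls are both included.
- Sample size and power: the calculation serves the "primary hypothesis that puberty will moderate the associations between brain network connectivity measures, and neuropsychiatric outcome in females post pTBI", so the claim is limited to patients.
- Aims and hypotheses, 1.4, hypothesis sentence: again path b, again limited to females after pTBI.

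**On the mediated effect of pTBI through connectivity (a × b)**
- Abstract, Methods: the model will "examine the moderating effects of puberty on the association between pTBI and neuropsychiatric symptoms"; the sentence then routes this association through network connectivity.
- Aims and hypotheses, 1.4, aim line: "Examine the moderating effect of puberty on the mediated association between pTBI, brain network connectivity and neuropsychiatric outcome".
- Analytical approach, Aim 1 paragraph: the main question is whether the size of the mediation effect depends on puberty stage at T0.

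**A third reading.** The last sentence of 1.4 explains the hypothesis as post-pubescent females differing from pre-pubescent females in their levels of connectivity, efficiency and outcome.

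The Aim 1 paragraph names PROCESS Model 59 with 95% bias-corrected intervals from 1000 resamples, and the rule "Confidence intervals that do not contain zero indicate significant effects" at p < .05. Exploratory analyses describes the primary model as examining the pathways one at a time. Secondary analyses fixes one primary outcome (a composite from the ASEBA summary scales) and one moderator coding (binary). The Mediator section defines a single change score for connectivity.

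**The concern.** Path-b moderation and moderation of the indirect effect are separate parameters, and one can be present without the other. If the sections disagree on which is primary, the answer to the primary question depends on which section is followed. Model 59 reports both, plus interactions on paths a and c', and the rule treats each effect alike at an unadjusted 5%. The choice of deciding effect therefore stays open until results are seen, although the sample size was set for one hypothesis "at a significance level of α = .05".

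The populations do not match either. The sample-size section limits path-b moderation to patients, but the standard model estimates it pooled over patients and controls.

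**Working it through.** **Inputs.** Design alpha 0.05 (Sample size and power); sidedness is not stated and two-sided is assumed from the 95% interval rule. Recruited 120, 60 per group, with about 20% attrition. The structure of Model 59 is the definition of the named method; the article does not write it out. The documents give no path values, so those below are assumptions.

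**The plan's own figure.** The plan gives no overall error rate for the moderation claim. Its sample size reproduces as 100 × 1.20 = 120, which leaves 120 × 0.80 = 96 evaluable. The 100 comes from a cited source, for power of at least .80 with an effect "corresponding to a value of 13% of the variance in predicted variable". It does not identify a contrast. With f² = 0.13/0.87 = 0.149, 80% power needs N = 55 for a 1-df test, 98 for 6 df and 104 for 7 df.

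**1. The two contrasts are different parameters.** With X = pTBI, W = puberty (0/1), M = connectivity score and Y = outcome, Model 59 fits

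- M = i₁ + a₁X + a₂W + a₃XW
- Y = i₂ + c₁X + c₂W + c₃XW + b₁M + b₂MW

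Path-b moderation is b₂. The indirect effect at W is (a₁ + a₃W)(b₁ + b₂W), so the post- minus pre-pubescence difference is

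(a₁ + a₃)(b₁ + b₂) − a₁b₁ = a₁b₂ + a₃b₁ + a₃b₂.

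- If only path a is moderated (b₂ = 0), the difference is a₃b₁, which can be non-zero while b₂ is zero.
- If only path b is moderated (a₃ = 0), the difference is a₁b₂, which is zero whenever a₁ = 0, whatever b₂ is.

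**2. The third reading is not moderation.** For the mediator in patients (X = 1), the post- versus pre-pubescence difference in level is a₂ + a₃. It contains a₂, the difference that healthy girls show too.

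**3. The population.** The outcome equation has no X × M term, so b₂ is pooled over patients and controls. It is not the patient-only effect named in the sample-size section.

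**4. False-positive rate if any path may carry the claim.** Three interactions (a₃, b₂, c₃), each at 5%, none truly present:

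1 − 0.95³ = 1 − 0.8574 = 0.1426, or 14.3%.

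This assumes independent tests, so it was checked by simulation with no true moderation:

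| Check | Any of three paths | b × puberty alone | Difference in indirect effects |
|---|---|---|---|
| t tests, N = 96 and 120, 10,000 runs per scenario, path values 0 to 1.5, 30% to 70% post-pubescent | 13.2% to 14.5% | 4.4% to 5.4% | not run |
| Bias-corrected bootstrap, 1000 resamples, N = 96, 600 runs, a = b = c' = 0 | 15.3% | 5.3% | 0.5% |
| Same, a = b = c' = 0.39 | 15.5% | 4.7% | 7.0% |

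With 600 runs the standard error near 14% is √(0.143 × 0.857/600) = 1.4 points, so the bootstrap results agree with 14%. Correlation between the tests hardly matters.

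**The case against.** The strongest reply is that 14% rests on a rule the article never states. The sentence on intervals excluding zero explains how to read a bootstrap interval; it does not say that one significant path is enough to claim that puberty moderates. The Aim 1 paragraph puts the main question as one contrast, the dependence of the mediation effect on puberty. This stands. A reader might infer that the plan runs a 14% error rate; the documents do not support that as a fact, only as an upper figure under one permitted reading.

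Three further points also stand:
- The Abstract is not a separate contrast, because its sentence continues through the mediator and so agrees with the Aim 1 paragraph.
- A reader might infer from the plural wording of the hypotheses that each network measure is run as its own mediator, multiplying the tests. The Mediator section speaks of one score used in all analyses, so that is not counted.
- A reader might want a rate at which the two contrasts disagree. That rate depends on path values the documents do not give, so none is claimed.

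Finally, testing order and adjustment are commonly left to an analysis plan, and the article cites a preregistration. That excuses a missing adjustment scheme. It does not excuse the contradiction, because the article itself names a primary hypothesis, a model and a significance rule, and its sections disagree on which effect the hypothesis concerns.

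**Conclusion.** The point holds as an inconsistency in the primary hypothesis. Two contrasts compete: path-b moderation, stated for patients in two places and for both groups in a third, and moderation of the indirect effect. The closing sentence of 1.4 adds a difference in levels that is not moderation. Nothing in the analysis section settles which decides.

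The cost in error rate depends on the reading:
- up to about 14% if any one path may carry the claim and none is truly moderated;
- about 5% if b × puberty alone decides;
- 0.5% to 7% in simulation for the difference in indirect effects, depending on the assumed paths.

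The article fixes the outcome and the moderator coding and defines one connectivity score, so the open choice is the contrast alone. It should be corrected before the data are analysed.

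**What to change.** In Sample size and power and in the Aim 1 analysis paragraph, name one deciding contrast, for the ASEBA composite and the single connectivity score.

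- The difference between the post- and pre-pubescence conditional indirect effects matches the question in the Abstract and the Aim 1 paragraph.
- If b × puberty is preferred, either state that it is pooled over patients and controls, or add the terms needed to estimate it in pTBI females.

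Then align the Abstract, the Introduction, hypothesis 1.4 (including its closing sentence), Sample size and power and the Aim 1 paragraph to that contrast. Apply the interval rule for the primary claim to that contrast only, and label the other path interactions as secondary. How the secondary effects are adjusted can be left to the analysis plan.

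The change is to wording only and needs no extra data. Its price is that moderation seen only on another path can no longer be claimed as confirmatory.
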